## Abstract

**Background:**

ANDROMEDA-SHOCK 2 is an international, multicenter, randomized controlled trial comparing hemodynamic phenotype-based, capillary refill time-targeted resuscitation in early septic shock to standard care resuscitation to test the hypothesis that the former is associated with lower morbidity and mortality in terms of hierarchal analysis of outcomes.

**Objective:**

To report the statistical plan for the ANDROMEDA--SHOCK 2 randomized clinical trial.

**Methods:**

We briefly describe the trial design, patients, methods of randomization, interventions, outcomes, and sample size. We portray our planned statistical analysis for the hierarchical primary outcome using the stratified win ratio method, as well as the planned analysis for the secondary and tertiary outcomes. We also describe the subgroup and sensitivity analyses. Finally, we provide details for presenting our results, including mock tables, baseline characteristics, and the effects of treatments on outcomes.

**Conclusion:**

According to best trial practices, we report our statistical analysis plan and data management plan prior to locking the database and initiating the analyses. We anticipate that this practice will prevent analysis bias and improve the utility of the study’s reported results.

## INTRODUCTION

Septic shock is a prevalent and lethal disease, with estimated mortality rates of approximately 40%.^1^Uncontrolled host response to infection results in a series of progressive derangements in circulatory homeostasis, including macro- and microcirculatory derangements, which lead to progressive tissue hypoperfusion, multiorgan dysfunction, and death.^2^

Prompt hemodynamic resuscitation is key for deactivating this vicious cycle. Tailored interventions such as fluids, vasopressors, and inotropes may improve this consumption‒delivery imbalance and possibly reverse this process.^3^However, each intervention has a narrow therapeutic index and is not free of adverse effects. Conversely, recently, the wide heterogeneity of hemodynamic patterns (i.e., vasoplegia, hypovolemia or cardiac dysfunction) and the emergence of peripheral perfusion as a relevant target of resuscitation have increased our understanding of the kinetics of septic shock resuscitation.^4,5^ Thus, personalization of therapy according to key macro- and microcirculatory parameters could aid in further improving patient-centered outcomes rseptic shock resuscitation.

The ANDROMEDA-SHOCK-2 is an investigator-led multicenter randomized controlled trial that integrates these physiological precepts into a resuscitation algorithm for early septic shock.^6^The objective of this manuscript is to outline the statistical analysis plan (SAP) of the trial with the aim of preventing sources of bias from exploratory analyses after the results are available. The SAP was developed following recommended guidelines prior to locking the trial database and starting analyses.

Our primary objective is to determine whether capillary refill time (CRT)-targeted resuscitation based on clinical hemodynamic phenotyping is associated with a decrease in a hierarchical composite outcome within 28 days after randomization, which includes mortality, time to cessation of vital support, and length of hospital stay, compared with standard care in patients with early septic shock.

Our secondary objectives are to determine whether CRT-targeted resuscitation based on clinical hemodynamic phenotyping is associated with a decrease in all-cause mortality, more organ support-free days, and a decreased length of hospital stay within 28 days after randomization compared with standard care in patients with early septic shock.

## METHODS

### Trial design

ANDROMEDA-SHOCK-2 is a prospective, multicenter, parallel-group, randomized trial that compares a 6-hour protocol of hemodynamic phenotype-based, CRT-targeted resuscitation *versus* standard care resuscitation in patients with septic shock. The trial protocol (version 1.0 from September 2021) was published and is registered with ClinicalTrials.gov (NCT05057611). The study is being conducted in 81 intensive care units (ICUs) in Latin America, North America, Europe, and Asia. The study was approved by the Ethics Committees of all the participating institutions. The main study interventions are summarized in figure 1.

**Figure 1 f01:**
[figure not shown]
Resuscitation strategies of the Intervention Group.

### Randomization

Eligible patients are randomly allocated to the intervention (CRT-P) or control (standard care) groups. A randomization sequence with an allocation of 1:1 is generated by a computer program. Study group assignment is achieved by means of randomized permuted blocks of variable size with stratification by center. Allocation concealment is maintained by means of central randomization via the web via Castor EDC®.

Because this is a nonpharmacological intervention, blinding the medical team is not feasible.

### Study interventions

Study interventions encompass a description of the general management for both groups, the CRT-P study protocol, the standard care group, and safety measures, all of which were previously delineated and elaborated upon in the literature.^6^

### Sample size

Given that the intervention arm includes several new steps aimed at better tailoring fluid administration, we expect a further decrease in the use of fluids. Based on ANDROMEDA-SHOCK data, this new algorithm could reduce fluid administration in at least 60% of these patients. Previous studies have shown that a reduction in fluid administration is associated with better outcomes. Thus, we estimate a 6% absolute reduction in mortality. The estimates of the number of days needing life support truncated at 28 days and the length of hospital stay in the Control Group were based on data from the ANDROMEDA-SHOCK Control Group.

For the Control Group, we assumed a 28-day mortality of 39%, number of days needing life support truncated in 28 days among survivors of 5.6 (standard deviation [SD], 6.7) and a length-of-hospital stay truncated in 28 days among survivors of 15.6 days (SD, 10.1). We considered that the experimental group treatment would reduce mortality to 33%, shorten the number of days of life support use among survivors to 4.3 (SD, 6.2) and shorten the length of hospital stay among survivors to 14 days (SD, 9.9).The length of hospital stay and the number of days needing life support were simulated assuming a beta-binomial distribution within 28 days via parameters acquired in the ANDROMEDA-SHOCK trial.^7^

Using the win ratio method with the three components listed above, with 1,500 patients enrolled, the trial will have a power of 88% to show superiority in the win ratio outcome for a two-sided α of 0.05. The study power was estimated based on 1,000 replications.

### Framework

The study design aims to demonstrate the superiority of the CRT-targeted strategy over the standard care strategy in terms of the hierarchical primary outcome (all-cause mortality within 28 days, time to cessation of vital support within 28 days, and length of hospital stay truncated at Day 28) using the win ratio method.

### Statistical interim analyses

Interim analyses are conducted after the inclusion of the first 200 patients and at 75% of the sample size (1,125 patients). Only the independent Data Safety Monitoring Board (DSMB) has access to the results of those analyses. The DSMB is formed by independent epidemiologists, intensivists, and a senior statistician. The DSMB established guidelines for stopping the trial for safety or efficacy. Stopping for safety will be considered if a p value < 0.01 comparing the primary outcome reveals harm for the experimental group compared with the Control Group in any of the interim analyses. Conversely, stopping for efficacy will be considered in the analysis with 75% of the sample size if there is a p value < 0.001 in favor of the experimental *versus* control treatment. According to the Haybittle–Peto rule, considering the strict p value threshold specified for the interim analysis (< 0.001), no further penalization is required for the final study analysis alpha value.

### Timing of final analysis

All outcomes will be analyzed simultaneously after we complete the 90-day follow-up of all patients, and the database will be locked.

### Timing of outcome assessment

We will assess outcomes at 6, 24, 48, and 72 hours; during the first 7 days until ICU discharge; at 28 and 90 days; and at ICU and hospital discharge.

### Statistical analysis principles

We will report two-sided p values for the primary outcome main analysis. If the experimental group strategy is superior to the Control Group for the primary outcome (p value < 0.05), we will test the treatment effect on the secondary outcomes in a hierarchical fashion at a significance level of 0.05. Ninety-five percent confidence intervals will be presented for all effect estimates. P values will not be presented for tertiary outcomes or other analyses. Owing to the risk of Type I error from numerous comparisons, the results for tertiary outcomes and other analyses should be considered exploratory.

### Adherence and protocol deviations

Protocol adherence will be described in a table reporting the numbers and percentages of nonadherence to the Intervention Group protocol and good clinical practice principles.

Protocol deviations will be assessed by a central clinical monitor for all centers. Major deviations are defined as incorrect inclusion, failure of informed consent, or inadequate resuscitation procedures regarding the CRT-P flowchart during the study period (first 6 hours). Minor deviations are defined as changes in the resuscitation procedures but with a clinically valid argument. This is shown in table 1S and figure 1S (Supplementary Material).

### Analysis populations

Analysis of the treatment effect on the primary outcome will consider an intention-to-treat population, defined as all participants who fit the inclusion and exclusion criteria, are randomized, and for whom there is consent for the use of data.^8-10^We do not anticipate substantial loss of follow-up for the primary outcome data. Nevertheless, eventual missing outcome data will be imputed via the chained equations method considering site, age, and baseline Acute Physiology and Chronic Health Evaluation (APACHE) II score. The conclusion of the trial will be based on the intention-to-treat analysis.

Analysis of secondary and other outcomes will consider the same intention-to-treat population, although no imputation will be carried out for patients lost to follow-up.

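### The set labelled intention-to-treat also requires eligibility, so read literally it drops patients found after randomisation to be wrongly included

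*SAP article*

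**What the plan says.** The section Analysis populations describes the primary analysis set, which it calls intention-to-treat, in these words: "defined as all participants who fit the inclusion and exclusion criteria, are randomized, and for whom there is consent for the use of data". It adds: "The conclusion of the trial will be based on the intention-to-treat analysis". For the rest: "Analysis of secondary and other outcomes will consider the same intention-to-treat population".

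The section Adherence and protocol deviations expects that some randomised patients will not have been eligible: "Major deviations are defined as incorrect inclusion, failure of informed consent, or inadequate resuscitation procedures regarding the CRT-P flowchart". On who judges this it says: "Protocol deviations will be assessed by a central clinical monitor for all centers". It does not say whether the monitor is masked to arm, when eligibility is settled, or what happens in the analysis to a wrongly included patient.

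The section Randomization states that "blinding the medical team is not feasible". The section Eligibility contains criteria that rest on judgement, among them refractory shock, framed as a high chance of dying within a day, and the attending clinician's view that aggressive resuscitation is unsuitable. The list of preplanned post hoc analyses includes a per-protocol analysis. No analysis of all randomised patients is described anywhere.

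**The concern.** Intention-to-treat normally means everyone randomised, analysed as allocated. Here eligibility is a further condition, alongside randomisation and data consent. A patient who is randomised, treated and followed, and then found not to have met a criterion, fails the definition. That is a modified intention-to-treat set, and the label tells readers that no such removal took place.

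Removing ineligible patients can be harmless if eligibility is judged only on data from before randomisation, by someone who does not know the arm. The article requires neither. Some criteria are open to hindsight: an early death could prompt the view that the patient was already in refractory shock at entry. Removal could then be linked to death, the first component of the primary outcome, and in an open-label trial it could also be linked to the arm. The wording permits this without showing that it would happen.

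**Working it through.** **1. The text, side by side.**

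- The definition joins three conditions: eligible, randomised, data consent. If the first merely repeated the second, no randomised patient could be ineligible.
- The deviations section provides for exactly such patients, so the first condition has work to do.
- The only other population mentioned is per-protocol. Apart from patients without data consent, no analysis brings back those whom the eligibility condition removes.

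**2. Size: inputs.** The plan gives no number of wrongly included patients, so there is no figure of its own to reproduce.

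- From the article (Sample size; Randomization): 1,500 patients at 1:1, so 750 per arm; 28-day mortality p of 39% in control and 33% in CRT-P; planned difference 6 points.
- Assumed: share e of an arm excluded, 1% to 3%; mortality m among those excluded, 60%, with 100% as an extreme.

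**3. Shift in observed mortality.** Mortality among those kept = (p − e·m)/(1 − e). For one arm with p = 0.33 and m = 0.60:

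- e = 1%: (0.33 − 0.006)/0.99 = 0.3273, a fall of 0.27 points (5% of the planned 6).
- e = 2%: (0.33 − 0.012)/0.98 = 0.3245, a fall of 0.55 points (9%).
- e = 3%: (0.33 − 0.018)/0.97 = 0.3216, a fall of 0.84 points (14%).

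With p = 0.39 and m = 0.60, mortality falls to 38.8%, 38.6% and 38.4%. With m = 100%, it falls to 38.4%, 37.8% and 37.1%.

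If both arms lose the same e at the same m, the difference becomes 0.06/(1 − e). At e = 2% this is 6.12 points against 6.00, so almost nothing changes.

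**4. Effect on the win ratio test when there is no true effect.** Simulation with 750 per arm and 6,000 replications. Both arms have control mortality and control durations, using beta-binomial distributions matched to the printed means and SDs. All pairs are compared by the plan's hierarchy, with two deaths a tie. Excluded patients have about 60% mortality.

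| Excluded, CRT-P | Excluded, control | Median win ratio | False superiority (nominal 2.5%) | Two-sided rejection |
|---|---|---|---|---|
| 0 | 0 | 1.001 | 2.8% | 5.2% |
| 1% | 0 | 1.005 | 3.4% | 5.4% |
| 2% | 0 | 1.010 | 3.4% | 5.0% |
| 3% | 0 | 1.016 | 4.2% | 6.0% |
| 4% | 1% | 1.016 | 3.5% | 4.9% |
| 2% | 2% | 1.000 | 2.6% | 5.1% |

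Monte Carlo error on the false-superiority column is about 0.2 to 0.3 points, so the 1% and 2% rows cannot be told apart, and neither lies far from the row with no exclusions. The simulation is unstratified, treats the two durations as independent, and uses a large-sample variance in place of the planned APACHE II strata and bootstrap.

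**5. Lost numbers are not the issue.** Under the planned effects, simulated power is about 99% at both 1,500 and 1,470 patients. It does not reproduce the plan's 88%, but the article prints neither the beta-binomial parameters nor the correlation between components. Only the comparison between the two sample sizes is used here, and the gap has no bearing on this point.

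**The case against.** The strongest reply is that the sentence only describes who enters the trial. It follows the order of enrolment, the screening and eligibility sections treat eligibility as a decision made before randomisation, and nowhere does the article say that a randomised patient is removed. Classing wrong inclusion as a major deviation carries no stated consequence for the analysis; inadequate resuscitation is in the same class, and nobody would infer that those patients leave the intention-to-treat set. The CONSORT figure and the supplementary deviation table and figure are not visible, and may report these patients by arm.

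This benign reading is possible. But the article does not adopt it, and a definition of the primary analysis set should not depend on which reading is chosen. Nor is this detail left to a fuller document: the article states the definition itself.

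A reader might infer two stronger things.

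- *That exclusions would be made knowing arm or outcome.* The documents do not show this. Only the medical team is said to be unblinded; the central monitor's masking and the timing of the review are not stated either way.
- *That CRT-P patients would be excluded more often because their records are checked more closely.* The adherence check concerns the CRT-P flowchart, but poor adherence is not a ground for leaving this set. Eligibility applies to both arms, and nothing suggests that it is checked more closely in one.

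It is also fair to say that consent for data use is itself a condition that can fail after randomisation. It differs in that data cannot be used without consent. The article says that it will seek that consent from patients who withdraw and will report those cases.

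**Conclusion.** The point holds as a defect in the definition of the primary analysis set. As written, the set is a modified intention-to-treat population under an intention-to-treat label. The primary and secondary analyses depend on it, with no stated safeguard on how eligibility is judged after randomisation.

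The likely harm is small and may be nil. Balanced exclusion of 2% per arm leaves the win ratio at 1.000 and false superiority at its nominal level within simulation error. One-arm exclusion of 1% to 3% at 60% mortality shifts that arm's mortality by roughly 0.3 to 0.8 points and takes false superiority from about 2.8% to 3.4–4.2%. The share excluded, its mortality and the imbalance are all assumptions; none comes from the article. The documents do not support saying that the trial's conclusion will in fact rest on biased exclusions. The case for changing the sentence is that it permits them, that the change is cheap, and that it must come before database lock so that the choice is not made with results in view.

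**What to change.** In Analysis populations, delete the condition that participants meet the eligibility criteria. Define the primary set as all randomised patients whose data may be used under consent, analysed in the arm to which they were allocated, whatever is later found about eligibility. Apply the same set to secondary and other outcomes.

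Keep the exclusion of wrongly included patients as a sensitivity analysis only, with eligibility judged blind to arm and on pre-randomisation data. Report by arm the number of wrongly included patients and the number without consent for data use, in the CONSORT figure if they are not already there.

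The cost is one sentence, one sensitivity analysis, and possibly a slight dilution of the effect by a few ineligible patients. If the authors meant only to describe who is enrolled, the edit changes nothing but clarity.

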## Analysis

### Outcome definitions

#### Primary outcome

The primary outcome of the study is a hierarchical composite outcome: (1) all-cause mortality within 28 days, (2) time to cessation of vital support truncated on Day 28, and (3) length of hospital stay truncated on Day 28.

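### The variables listed for imputing the missing primary outcome leave out treatment arm and what was known up to loss, so imputed values dilute the treatment effect by about the missing fraction

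*SAP article*

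**What the plan says.** The imputation rule is in the SAP article under Analysis populations: "missing outcome data will be imputed via the chained equations method considering site, age, and baseline Acute Physiology", the last item being the baseline APACHE II score. The same section says of the amount of missing data: "We do not anticipate substantial loss of follow-up for the primary outcome data". It gives no percentage. It also makes this the analysis that decides the trial: "The conclusion of the trial will be based on the intention-to-treat analysis".

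The outcome to be imputed has three tiers: "1) all-cause mortality within 28 days, (2) time to cessation of vital support truncated on Day 28, and (3) length of hospital stay", the last truncated on Day 28 (Primary outcome). Information accrues well before Day 28: "We will assess outcomes at 6, 24, 48, and 72 hours; during the first 7 days until ICU discharge", then at 28 and 90 days and at ICU and hospital discharge (Timing of outcome assessment).

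No other section names a further variable for the imputation model.

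**The concern.** The primary analysis compares two arms, so an imputation model compatible with it has to let the outcome differ by arm. With only site, age and APACHE II as listed, a missing outcome in the CRT-P group and one in the control group are drawn from the same distribution for patients with the same covariates. The imputed part of the data then shows no treatment effect, whatever the true effect is, and the combined estimate is pulled toward a win ratio of 1.

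The list also leaves out what was known up to loss, such as survival to a given day or hospital days already accrued. An imputed value could then conflict with an observed fact.

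At stake is some dilution of the estimate, and hence some loss of power, in the analysis that carries the trial's conclusion.

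**Working it through.** **Inputs from the SAP article**
- Control mortality: "For the Control Group, we assumed a 28-day mortality of 39"%; the experimental arm is assumed at 33% (Sample size). The difference is 6.0 points.
- Allocation: "A randomization sequence with an allocation of 1:1 is generated by a computer program" (Randomization). The pooled risk is therefore (39 + 33)/2 = 36%.
- Among survivors, control versus experimental: days of life support 5.6 (SD 6.7) versus 4.3 (SD 6.2); hospital stay 15.6 (SD 10.1) versus 14 (SD 9.9). Beta-binomial within 28 days; 1,500 patients (Sample size).
- Stated power: 88% at two-sided 0.05.

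**Assumed.** The missing fraction f, shown from 1% to 20%. Loss is completely at random and equal in both arms. Site, age and APACHE II are balanced by randomization, so the covariate-specific draws average to the pooled risk in each arm.

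**The plan's own figure.** The plan gives no figure for the effect of imputation. Its 88% power was not reproduced. An all-pairs win ratio with independent, moment-matched beta-binomial components gives about 99% power (win ratio 1.34). The settings behind the 88% are not shown, so this is not counted as an error. The attenuation below is a ratio and does not depend on it.

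**Step 1: mortality, arm omitted**

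CRT-P risk = 33(1 − f) + 36f; control risk = 39(1 − f) + 36f; difference = 6(1 − f).

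- f = 1%: 38.97 − 33.03 = 5.94 points.
- f = 5%: 38.85 − 33.15 = 5.70 points.

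**Step 2: win ratio, arm omitted**

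With equal loss, the CRT-P group becomes a mixture with share 1 − f/2 from the CRT-P distribution, and the control group has share f/2 from it. The gap in shares is 1 − f. Win and loss probabilities came from simulated populations of 4 million per arm.

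| f | Mortality difference (points) | Win ratio | Log win ratio relative to no missing data |
|---|---|---|---|
| 0 | 6.00 | 1.337 | 1 |
| 1% | 5.94 | 1.334 | 0.99 |
| 2% | 5.88 | 1.330 | 0.98 |
| 5% | 5.70 | 1.318 | 0.95 |
| 10% | 5.40 | 1.299 | 0.90 |
| 20% | 4.80 | 1.261 | 0.80 |

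**Step 3: arm included.** In trial-size simulations (750 per arm, 10 imputations, 1,000 replications), drawing donors within arm left the win ratio at 1.33 to 1.34 at every f. Drawing from pooled donors gave 1.321 at 5% and 1.298 at 10%, in line with Step 2.

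**Step 4: approximate power, anchored on the stated 88%**

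The noncentrality is 1.960 + 1.175 = 3.135, and power = Φ(k × 3.135 − 1.960). With arm included, k = √(1 − f). With arm omitted, k = 1 − f if the standard error is unchanged, and k = (1 − f)^1.5 if it grows as under Rubin's rules. Both are shown because the plan uses a bootstrap.

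| f | Arm included | Arm omitted |
|---|---|---|
| 1% | 87.7% | 87.0 to 87.4% |
| 2% | 87.4% | 86.0 to 86.7% |
| 5% | 86.3% | 82.7 to 84.6% |
| 10% | 84.5% | 76.3 to 80.6% |
| 20% | 80.1% | 61.2 to 70.8% |

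**The case against.** The strongest reply is that the effect hardly matters. The plan expects little loss, and at 1% to 2% missing the win ratio moves only from 1.337 to 1.334 or 1.330. All outcomes are analysed after 90-day follow-up, and a patient found alive at 90 days has a known 28-day survival status, which limits missing data in the first tier. With similar loss by arm the bias is toward no effect and does not by itself inflate the type I error. All of this stands and sets the size of the point. It does not remove the point: the stated list omits arm, and including it costs nothing.

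A reader might also infer more than the document supports:

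- **That only these three variables are used and all follow-up data are ignored.** The text says *considering*, not *only*. Chained equations normally condition each incomplete component on the others, so observed tiers may inform missing ones. The plan does not say so, and this would not directly bring in arm.
- **That a patient known to have left hospital alive would be assigned death at a flat 36%.** The model conditions on site, age and APACHE II, so the draw is at a covariate-specific risk. The 36% in Step 1 is an average over an arm.
- **That site is too sparse to use.** The plan does not say how site enters. 1,500 patients over 81 ICUs is about 18.5 per site on average, and randomization is stratified by center, so including site is defensible. No failure of the model is shown.
- **That primary and secondary mortality contradict each other.** For secondary and other outcomes the plan says "although no imputation will be carried out for patients lost to follow-up". Secondary mortality uses a Cox model, which can censor at last contact, whereas the win ratio needs a binary 28-day status. The different handling is stated openly and is defensible.

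**Conclusion.** The point holds as a defect in the stated imputation list. Followed as written, imputed primary outcomes carry no treatment effect, and the log win ratio shrinks by about the missing fraction: roughly 1% at f = 1% and 5% at f = 5%. The loss is negligible at 1% to 2% missing and becomes noticeable from about 5%.

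These sizes rest on an assumed f, similar loss in both arms, data missing at random, and the plan's own effect assumptions with independent components. Under those conditions the consequence is lost power and a diluted estimate, not a false positive. The document does not support a claim that the primary result is seriously threatened.

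**What to change.** Amend the imputation sentence under Analysis populations before database lock:

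- Impute within each arm, or include treatment arm in the imputation model.
- Name the three outcome components as variables in the model, together with the status at last contact where it is recorded.
- Keep imputed values consistent with observed facts: for example, alive up to last contact, and a stay at least as long as already observed.

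Arm is known for every randomized patient and the outcome components are already collected. The article does not show whether the date and status of last contact are recorded, hence the qualifier. The cost is a sentence or two in the SAP and a slightly larger imputation model, with no change to sample size or data collection.
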